## Methods/Design

### Design

We plan a pilot cluster, randomised, controlled trial conducted in 14 care homes for older people over 24 months, an embedded health economic feasibility study, and individual and focus group interviews to investigate sustainability and integration of the intervention.

### Population

The study will be conducted within the boundaries of Bradford Metropolitan District Council, West Yorkshire, in the north of England.

#### Inclusion criteria for care homes

The inclusion criteria for care homes will be as follows:

1. Care homes for older people in Bradford (nursing and residential)

2. Run by an independent provider (private, voluntary or non-profit making)

3. Within catchment area for Bradford District Care Trust Older People’s Community Mental Health Teams

#### Exclusion criteria for care homes

The exclusion criteria for care homes will be as follows:

1. Local Authority homes - these are homes run by local government. The number of care homes for older people run by local authorities is decreasing and the money is being transferred to third party providers. Therefore, it is believed that the intervention is less likely to be implemented in local authority homes.

2. Specialist homes (those focusing on stroke rehabilitation, except for those specialising in providing dementia care)

3. Care homes involved in other projects likely to impact on study (initiatives to reduce hospital admissions)

#### Inclusion criteria for residents

All residents present in the care home at the time of baseline assessments will be considered for participation.

#### Exclusion criteria for residents

The exclusion criteria for residents will be as follows:

1. Unable to participate in assessments because of severe communication difficulties or severe dementia.

2. Receiving end-of-life care

3. Non-English speakers

Whilst we recognise that the exclusion of non-English speakers is restrictive, we feel that it is appropriate at this trial stage. The number of Black and Minority Ethnic elders in Bradford care homes is thought to be low and the validated assessment tools are not available in South Asian languages. Recruitment will be monitored to ascertain how many people are excluded for this reason to inform the inclusion criteria of a future trial.

### Sample size

For a definitive trial, in the absence of empirical data on which to base an estimate of effect size from care homes, we plan to extrapolate from results obtained in hospital studies [9,10]. This approach is reasonable given similarities in the population and processes of care. Although care home residents may be less physically unwell, limiting the scope for impact, this is balanced by increased opportunity for staff to benefit from training and improve practice [17,28] and for residents to receive greater benefit due to longer exposure staff practice changes than is the case for short admission spells in hospitals.

For an individually randomised trial, 809 participants would be required per group to provide 80% power at 5% significance level to detect a reduction of one-third in delirium rates (found in delirium prevention studies in hospital settings). The assumed control rate of delirium is 14% (the median-point prevalence of delirium found in our literature review [8]).

The attrition rate would reduce the number of participants with a valid outcome within a site (cluster) and therefore affects the cluster size. When designing a cluster randomised trial, the cluster size, together with the intraclass coefficient (ICC), is used to estimate the design effect, which increases the sample size (compared to an individually randomised trial) to account for the clustering of outcomes.

### Recruitment

#### Care home recruitment

Eligible care homes in the Bradford District will be identified from the Care Quality Commission (CQC) public listing and the managers invited to return an expression of interest (EOI) in the study by post. Homes returning a positive EOI and non-respondents will be followed up with a telephone call. Care home managers who confirm their interest or have further queries will be visited in person to explain the study objectives, timescales and involvement required.

#### Resident recruitment

Care home managers will be asked to identify eligible residents in their care home. For those clearly not eligible, the following non-identifiable data will be recorded: care home, age, sex, ethnicity, and reason for exclusion.

All eligible residents will be asked by care home staff if they are willing to be seen by researchers so they can explain the study. If they agree, a researcher, accompanied by a member of care home staff will then explain the study to the resident and assess for capacity to consent. If residents have capacity they will be asked for consent to participate in the study. Residents who consent will also be asked about their views on future participation should their capacity fluctuate (through worsening dementia or a delirious episode). For residents without capacity, the advice of a consultee will be sought if there is no advanced directive in place pertaining to participation in research.

A protocol amendment has been put in place in order to undertake further recruitment of residents at 12 months post-intervention (2 to 4 months prior to the outcomes assessments). This will mitigate the effect of attrition in this extremely frail and elderly population and subsequent loss to follow-up. It will also allow us to investigate the feasibility of alternative approaches to the timing of recruitment.

Additional recruitment will take place in all care homes participating in the study. Care will be taken to spread additional recruitment over both the intervention and control arms. Residents will only be considered for recruitment at this stage if they have moved into the home subsequent to the first round of recruitment (those who have already been approached and refused will not be approached again). All other eligibility criteria will apply.

Additional residents will be recruited during the intervention and will provide baseline and follow-up assessment data in the same way as those recruited earlier.

We are conscious that a two-tier recruitment strategy may lead to differential recruitment, as randomisation to the intervention or control arm has already taken place; however, additional recruitment will not be used as a covariate in analyses.

### Randomisation

Homes will be randomised on a 1:1 basis to receive either active intervention (Stop Delirium!) or control (usual care) by the Leeds Clinical Trials Research Unit (CTRU), stratified by care home size (<20 or under, ≥20 residents) and the percentage of residents with dementia (<62%, ≥62%). Randomisation will take place only after the baseline recruitment and assessment of residents have been completed for each home.

### Blinding

Due to the nature of the intervention, it will not be possible to blind participants or the research team to allocation. Outcome measures will be collected by researchers having no role in the intervention and having no explicit knowledge of the allocations.

### Intervention

#### Stop Delirium!

Intervention homes will receive the Stop Delirium! package. This is a multicomponent intervention designed to prevent delirium in care home residents, based on the best delirium prevention and practice change evidence. It aims to modify key resident and environmental delirium risk factors (pain, infections, dehydration, poor nutrition, constipation, polypharmacy, sensory impairment, limited mobility and sleep disturbance) by improving the quality of care. A specialist delirium practitioner (DP) leads a delirium prevention educational process such that care home staff feel empowered, develop relevant skills and are able to identify opportunities for delirium prevention through the development of local care pathways and solutions tailored to the home environment. Key components (tested and refined in our previous feasibility study [22]) include:

1. Three 20-minute small group interactive education sessions for all staff in the home delivered by the DP and then offered monthly to new staff.

2. Monthly Staff Working Groups facilitated by the DP to identify key priority areas for delirium prevention in the home. Participants are drawn from staff volunteers attending education sessions.

3. A Delirium Box containing educational and implementation materials is established in each home by the home manager, supplemented by bespoke materials produced by staff members of the care home Working Groups.

4. The identification of delirium champions by the DP, who are then trained to deliver the education sessions and to facilitate Staff Working Groups under supervision, with a view to sustaining the intervention.

5. A manualised intervention to provide a consistent educational experience and approach to developing the workshops. Specific features of the intervention can be found on the European Delirium Association website [29].

The intervention will be in place for 16 months. This is 6 months longer than was allowed for in the previous feasibility phase. This period is intended to provide sufficient time for any change in practice to embed and have an effect.

#### Control

Residents in control homes will receive ‘usual care’ during the study but care homes will be offered the intervention at study end.

### Outcomes

Outcomes aligned to the feasibility objectives and research questions are detailed in Table 1.

### Data collection

Data will be collected electronically at each of the 14 care home sites, using portable, password-protected, encrypted devices (tablets). Each tablet will be configured to ease the burden on residents by allowing pre-population of data fields (where information has already been gathered by another assessment tool) and to allow intermittent breaks in data collection if necessary. System checks will flag all missing data to the researcher in real time which will ensure that the data sets are as complete as possible.

For each home in the study the following information will be recorded at baseline:

#### Care home data

Data collected from the care home records will include:

1. Name of provider.

2. Type of care (nursing only or nursing and dementia).

3. Number of residents.

4. Number of staff, including skill mix.

5. Hospital admissions over the previous 6 months.

6. Falls over the previous 6 months.

7. Any current educational programmes or other relevant initiatives.

#### Resident data

Screening and baseline data for residents will be collected before randomisation. Post-intervention outcome data will be collected at 16 months post-randomisation.

### Screening

The following anonymised screening, information will be collected for all residents within the care home: gender, age, ethnicity and eligibility for inclusion. Reasons for non-eligibility will be recorded.

### Baseline assessments

For all residents recruited, the following information will be recorded through examining care home records or administering tests. Baseline assessment data will include:

1. Initials

2. NHS number and hospital ID

3. GP name and address

4. Age

5. Sex

6. Medications - total number and names

7. Co-morbidities (Charlson index [30])

8. Activities of Daily Living (ADL) [31]

9. Hearing Impairment

10. Visual impairment (Snellen test card at 3 meters, acuity below 6/18 assessed as visually impaired)

11. EuroQoL EQ-5D and EQ5D proxy [23]

12. Either the Social Care Related Quality of Life (SCR-QoL) [24] or Dementia Quality of Life DEMQOL and DEMQOL-Proxy [25]

13. Delirium

Delirium assessments will be undertaken using a three step process:

1. Assessment of cognitive impairment using the Six Item Cognitive Impairment Test (6-CIT) [32,33]

2. Short Confusion Assessment Method (CAM) [26]

3. In those screening positive on CAM, the Delirium Rating Scale Revised-98 (DRS-R-98) [27] (using a cut-off score of >17.75)

### Post-intervention assessments

Researchers, blind to allocation, will collect data 16 months from randomisation - deemed to be the start of the intervention - through administering tests on alternate days (except Sundays) for a period of one month and examining individual care home and hospital records. Researchers will record;

1. Presence of delirium on any day during a 1-month post-intervention period. Screening will use the 6-CIT and short version CAM. Presence or absence of delirium for those positive will be confirmed using the DRS-R-98 (as at study baseline). Ratings for a 10% subsample will be compared to determine inter-rater reliability.

2. Delirium severity (proportion of residents with DRS-R-98 severity scale score >15.25 at any assessment) during the 1-month post-intervention period.

3. Delirium duration (days positive for delirium) during the 1-month post-intervention period.

4. Number of medications.

5. Activity of Daily Living (ADL) scores.

6. Falls during previous 6 months.

7. Mortality during previous 6 months.

8. Hospital admissions during previous 6 month including;

a. total length of stay

b. number of admissions

c. time to first admission

The 6-CIT is a dementia screening tool used in primary care. The short CAM is a four-question instrument used extensively for delirium screening and diagnosis [26]. The DRS-R-98 is a valid measure of delirium occurrence and severity [27]. We know that the training of the researcher affects performance of these instruments [34]. Researchers will be trained before both the baseline and post-intervention assessments. As part of the analysis, we will also check inter-rater reliability at baseline by comparing ratings for a 10% subsample.

If a resident scores positive on the short CAM, indicating a possible delirium, subject to prior consent, the care home manager will be informed in writing on the day of assessment so that appropriate action can be taken. A copy of this letter will be held on file with the consent forms.

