	What are the costs from the perspective of the service provider (health and social care) associated with delirium and with Stop Delirium?	
**Scientific:** To determine the most appropriate method to capture resource use in this setting and population and costs of delirium and of delivering the intervention	Can a high (>90%) coverage for delirium screening be achieved using the short Confusion Assessment Method (CAM) [26]? And can a high completion rate (>90% complete) be achieved for the Delirium Rating Scale-Revised (DRS-R-98) [27] in those positive for CAM? Is delirium be determined reliably (>90% inter-rater reliability) using these instruments?	Delirium severity: proportion of residents with severe delirium during a one-month period
		Delirium duration (days positive for delirium) during a one month period
		Delirium incidence on any on any day during a one-month post-intervention period
		Mortality during previous 6 months
		Hospital admissions during previous 6 months including total length of stay, number of admissions, time to first admission
	What are the rates of delirium and admission to hospital in residents in intervention homes compared to control homes post intervention? And which measure yields more complete hospital admission data: length of stay, number of admissions or time to admission?	
To estimate the rates of delirium and hospital admissions in intervention and control homes	What is the intraclass coefficient (ICC) for the proposed primary outcome, delirium occurrence?	The primary outcome for this study is the presence of delirium on any day during a one-month post intervention period determined by screening with short version CAM [26] on alternate days (except Sundays) and confirmed for those positive or borderline using the Delirium Rating Scale-98 (DRSR98) [27].

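### The severe delirium outcome does not require confirmed delirium, so a resident who is a non-case on the primary outcome can be counted as severe

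*Protocol article*

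**What the plan says.** Delirium is assessed in steps, ending with the DRS-R-98. The Baseline assessments section gives the confirmation rule: "In those screening positive on CAM, the Delirium Rating Scale Revised-98 (DRS-R-98) [27] (using a cut-off score of >17.75". The Post-intervention assessments section, item 1, carries it forward: "Presence or absence of delirium for those positive will be confirmed using the DRS-R-98 (as at study baseline". Table 1, in its entry for the primary outcome, describes a slightly wider group: "confirmed for those positive or borderline using the Delirium Rating Scale-98 (DRSR98".

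Item 2 of the Post-intervention assessments section defines severity: "Delirium severity (proportion of residents with DRS-R-98 severity scale score >15.25 at any assessment". Table 1 lists this outcome under the scientific objective as "Delirium severity: proportion of residents with severe delirium during a one-month period".

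The same instrument serves both purposes: "The DRS-R-98 is a valid measure of delirium occurrence and severity [27". The article names a severity scale for the 15.25 cut-off. It does not name the DRS-R-98 score to which 17.75 applies, and it gives no range or item make-up for either score.

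**The concern.** A resident labelled as having severe delirium should first have delirium. Item 2 sets a threshold, a population (residents) and a time rule (any assessment), but it does not make confirmation a condition. Everyone who is given the DRS-R-98 after the screen can therefore enter the severe count, including those whom the DRS-R-98 then fails to confirm.

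The next item, duration, does count only days positive for delirium, so the article ties one of the two neighbouring outcomes to case status and not the other.

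At stake is whether the occurrence and severity outcomes are consistent with each other. If the rule is followed as written, one resident can be a non-case on the first and a severe case on the second, and the severe group need not be a subset of the delirium group. A pilot meant to inform the design of a definitive trial should not hand on an outcome with that property.

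**Working it through.** The plan states no figure for this point, so there is none to reproduce. The check is an enumeration of score combinations.

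**Inputs from the document**
- Confirmed delirium: DRS-R-98 score T > 17.75 (Baseline assessments; applied again after the intervention).
- Severe: severity scale score S > 15.25 at any assessment (Post-intervention assessments, item 2).
- Given the DRS-R-98: CAM-positive residents, or CAM-positive and borderline residents according to Table 1.

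**Assumptions, not in the document**
- Scores are whole numbers, so confirmed means T ≥ 18 and severe means S ≥ 16.
- The severity scale is nested in the score used for confirmation: T = S + D, where D is the points from other items and runs from 0 to a maximum m. The article does not give m, so it was varied from 0 to 10.

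**Step 1: severe but not confirmed.** This needs S ≥ 16 and S + D ≤ 17. The solutions (S, D) are:
- (16, 0), total 16
- (17, 0), total 17
- (16, 1), total 17, available once m ≥ 1

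At least two of these exist for every m from 0 to 10, so the possibility does not depend on the size of the non-severity part. It does depend on D: with D ≥ 2, S ≥ 16 gives T ≥ 16 + 2 = 18, and the resident is confirmed.

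**Step 2: confirmed but not severe.** This needs S ≤ 15 and S + D ≥ 18, so D ≥ 3, and T lies between 18 and 15 + m.

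| Maximum points outside the severity scale (m) | Totals at which a confirmed case can be non-severe |
|---|---|
| 0 to 2 | none |
| 3 | 18 |
| 5 | 18 to 20 |
| 6 | 18 to 21 |
| 7 | 18 to 22 |
| 10 | 18 to 25 |

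The share of confirmed cases that would be non-severe thus runs from zero (m ≤ 2) to an amount that depends on m and on the distribution of scores. The document gives neither, so no proportion can be derived.

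**The case against.** The strongest reply is that the labels already settle the matter. Table 1 speaks of severe delirium and item 2 is headed delirium severity, so a sensible analyst would apply the threshold to residents with delirium. A condensed article may also leave derivation rules to a fuller document. This has some force: the intended meaning is probably the restricted one. But the article does not leave the rule open. It states the threshold, the population and the any-assessment rule, and those words, followed exactly, admit unconfirmed residents.

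A second reply is that the conflicting group is narrow. It consists of three combinations, and the resident must have reached the DRS-R-98 through the screen while scoring 0 or 1 on everything outside the severity scale. That stands, and it limits the size of the problem.

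A third reply is that little hangs on it. The Analysis section restricts the quantitative work to description and interval estimation, and the primary outcome, its ICC and the sample size do not use 15.25. That also stands.

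A reader might go further and infer that, because 15.25 is smaller than 17.75, the severe threshold lies below the threshold for delirium itself and almost every confirmed case will be severe. The documents do not support this. The 15.25 belongs to a named severity scale and the 17.75 to an unnamed DRS-R-98 score, so the two numbers cannot be compared as points on one scale. Step 2 shows that the share of severe cases could be anything from all of them downwards, depending on quantities that are not given. For the same reason it cannot be said that the severity outcome merely repeats the occurrence outcome.

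**Conclusion.** The point holds in a limited form. As written, the severe delirium outcome is not conditional on confirmed delirium, and a CAM-positive or borderline resident whom the DRS-R-98 did not confirm can be counted as severe. Under whole-number scores and a nested severity scale, this happens at severity 16 or 17 with a total of 17 or less, whatever the number of points available outside the severity scale. The number of residents affected is unknown and may be small. The proportion of confirmed cases below the severe cut-off is not determinable from the document.

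This is a minor correction to a secondary, descriptive outcome. It is still more than a missing detail, because the stated rule can misclassify residents when it is followed exactly.

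**What to change.** Four wording changes:
1. Count a resident as having severe delirium only if the severity score exceeds the stated cut-off at an assessment where delirium was also confirmed.
2. Keep all screened residents as the denominator for the between-arm proportion, as the Outcome assessments section does for delirium occurrence.
3. Name the DRS-R-98 score to which each of the two cut-offs applies, and reconcile Table 1 with the other sections on whether borderline residents are given the DRS-R-98.
4. Add a descriptive summary by arm of the peak severity score among confirmed cases. A proportion of all residents falls when episodes are prevented, even if the remaining episodes are no milder, so it cannot show severity on its own.

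The cost is small. The data are already collected and no further assessment is needed. The severe count may be slightly smaller. The summary among cases must stay descriptive, because it conditions on having delirium, which arises after randomisation, so the two arms' cases need not be comparable.

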#### Acceptability and burden of assessments

Time taken for completion of assessments will be recorded contemporaneously. Rates of completion for all outcomes measures or reason for noncompletion will be recorded. In addition, note will be taken of who completes the health-related quality of life measures (residents or proxies (carer or relative)).

#### Treatment data

*Intervention compliance.* Adherence to the components of the intervention at 4, 8 and 16 months from randomisation - early middle and late phases of delivery - will be recorded using a standardised *pro-forma*. Data recorded will include degree of completion for each component (education sessions, working groups) and reasons for noncompliance, allowing calculation of adherence rates for each, and identification of components that may need alteration before use in a definitive trial.

*Concomitant interventions.* Any new initiatives or projects introduced during the study period by other agents (researchers, health organisations or local authorities-especially those aimed at reducing hospital admissions and falls - will be recorded at 4, 8 and 16 months from randomisation).

